## Abstract

**Background:**

Intraoperative hypotension (IOH) is a common complication in non-cardiac surgeries, with significant impacts on postoperative outcomes such as acute kidney injury (AKI), myocardial injury after non-cardiac surgery (MINS), and postoperative cognitive dysfunction (delirium). Traditional non-invasive blood pressure monitoring often results in blind gaps through the discontinuous measurement, potentially missing critical hypotensive events. This study investigates the efficacy of a non-invasive, continuous AI-supported technology using the Hypotension Prediction Index (HPI) system, designed to predict and mitigate IOH, in reducing the incidence and severity of IOH and related complications in major orthopedic and trauma surgeries.

**Methods/design:**

This monocentric, randomized, prospective interventional trial will be conducted at the University Hospital Giessen. The study will include patients aged 45 years and older undergoing major orthopedic or trauma surgeries. Participants will be randomized into two groups: an intervention group receiving hemodynamic management using the ClearSight system in combination with a HPI-based treatment algorithm and a control group receiving standard care. The patients from the standard group also receive continuous cardiac output monitoring; however, this will be blinded to the anesthesiologist, to ensure the comparability of the measured hemodynamic parameters. The primary endpoint is the incidence, duration and severity of IOH, which is defined as MAP < 65 mmHg for at least one minute and which is calculated as the area under MAP < 65 mmHg and the time-weighted average (TWA) of MAP < 65 mmHg. Secondary endpoints include the occurrence of postoperative AKI (measured by KDIGO criteria), MINS (measured by high-sensitivity troponin I assays), and postoperative delirium. The study aims to recruit 150 patients, accounting for potential dropouts, to provide sufficient power to detect differences in the primary and secondary endpoints.

**Conclusion:**

This study aims to demonstrate improved intraoperative hemodynamic stability, with a reduction of hypotension and a reduced incidence of postoperative complications, potentially setting a new standard for non-invasive continuous monitoring in orthopedic and trauma patients.

**Trial registration:**

ClinicalTrials.gov NCT06291714. Registered on 4 March 2024.

**Supplementary Information:**

The online version contains supplementary material available at 10.1186/s13063-025-09194-x.

## Introduction

### Background

Blood pressure monitoring is a critical component of perioperative hemodynamic assessment. On the other hand, hypotension is not clearly defined as shown in previous studies [1]. Some studies defined hypotension as a systolic arterial blood pressure (SAP) below 100 mmHg or a mean arterial pressure (MAP) below 60 mmHg [1, 2]. Intraoperative hypotension (IOH) frequently occurs during non-cardiac surgeries and is associated with an increased risk of postoperative complications such as acute kidney injury (AKI) and myocardial injury after non-cardiac surgery [3]. Therefore, and as described above, the occurrence of hypotension displays a common intraoperative complication. The reasons can be found in vasodilatation, reduced inotropy (e.g., drug induced), bradycardia, or intravascular volume deficit (based on preoperative fasting and intraoperative blood loss). Main factors causing IOH are age, preexisting diseases (e.g., ASA > 3), duration of surgery, acuteness of surgery (e.g., emergency), anti-hypertensive medication, and anesthesia combining general, regional anesthesia, and preoperative baseline blood pressure [4, 5].

Complications related to IOH can be detected in most organ systems of which renal failure poses a relevant complication in the perioperative phase. AKI affects up to 25% of patients attending the intensive care unit (ICU) [6]. Liu et al. showed that even an episode of relative IOH is commonly associated with the occurrence of a postsurgical AKI (a decrease in SBP relative to preoperative value displayed a significant independent predictor of the development of AKI and of RIFLE classes I and II; odds ratio 1.084 for every − 1 mmHg change in SAP) [7]. As they state, “normotensive renal failure” is not common and is a rare phenomenon in the absence of septic and other complications. Traditional methods of blood pressure monitoring rely on intermittent measurements, which can miss critical hypotensive episodes due to "blind" intervals where no data is collected [8]. These intermittent measurements often fail to provide the necessary information for immediate intervention, leading to a higher incidence of IOH and its adverse consequences.

The failure to detect IOH using traditional methods is a significant problem, as IOH is correlated with substantial postoperative complications. IOH is particularly dangerous in orthopedic and trauma surgeries, where stable hemodynamic conditions are crucial for the success of the operation and the patient’s recovery. Studies have shown that even short periods of IOH can result in serious postoperative complications. For instance, Salmasi et al. demonstrated that IOH (defined as mean arterial pressure < 65 mmHg) is associated with higher rates of AKI and myocardial injury, underscoring the need for improved intraoperative blood pressure monitoring [9].

The ClearSight Hypotension Prediction Index (HPI) system is a non-invasive continuous hemodynamic monitoring (Edwards Lifesciences). This AI-supported system is capable of predicting hypotensive events, with a median lead time of approximately 2–3 min in clinical practice, although under certain conditions predictions of up to 15 min in advance have been reported. This capability allows anesthesiologists to take preventive measures before IOH occurs, thereby reducing the risk of complications. The predictive ability of the HPI system has been validated in previous studies [10], and earlier trials demonstrated that its use was associated with a significant reduction in intraoperative hypotension [11–13]. By enabling proactive management of hemodynamic stability, the ClearSight HPI system has the potential to significantly improve patient outcomes in major orthopedic and trauma surgeries. The HPI software is commercially available.

### Study hypotheses

#### Primary hypothesis

The perioperative use of non-invasive HPI-guided goal-directed therapy (GDT) reduces the incidence, and severity of IOH in patients undergoing major trauma and orthopedic surgery.

#### Secondary hypotheses

The use of HPI-guided GDT reduces the occurrence of postoperative renal failure and postoperative myocardial injury. Furthermore, the incidence of postoperative delirium can be reduced.

### Study objectives

The primary objective is to investigate whether HPI-guided GDT can reduce the incidence, duration, and severity of IOH in comparison with no GDT. Secondary objectives include assessing the impact on postoperative renal failure, myocardial injury, and delirium.

## Methodology

### Study design

This is a randomized, prospective interventional trial comparing continuous non-invasive cardiac output monitoring (ClearSight system) to standard care. The study will take place at the university hospital Giessen and Marburg, Giessen, Germany. The study protocol has been approved by the local ethics committee (EA 70/21). This trial has been registered with the NIH, U.S. National Library of Medicine at ClinicalTrials.gov (NCT06291714) on 4 March 2024. This article adheres to the Standard Protocol Items: Recommendations for Interventional Trials (SPIRIT) statement (Additional file 1) [14].

### Study population

The study will include patients aged 45 years and older undergoing major orthopedic or trauma surgery, such as reconstructive surgery of the pelvis (e.g., stabilization of fractures), total hip or knee arthroplasty, surgery of the proximal femur (e.g., stabilization of fractures), and surgery of the spine in a supine position. A further inclusion criterion is a planned anesthesia time of > 90 min in general anesthesia. Exclusion criteria include invasive blood pressure monitoring, participation in another interventional study, pregnancy and nursing mothers, surgery without controlled mechanical ventilation, patients with ASA I or IV, preexisting arterial fibrillation and known allergy against gelatine.

### Preoperative management

Patients are recruited before surgery after checking inclusion and exclusion criteria by the dedicated study team. Informed consent is obtained at this time from a study team member. Patients will be randomized 1:1 to the two groups after achieving the patient’s informed consent. Randomization will be performed using computer-generated random numbers and will be performed by the study team. Further, the following basic characteristics are obtained:Age, sex, height, weight, ASA scorePre-existing conditions (hypertension, coronary heart disease with and without history of myocardial infarction, peripheral arterial disease, renal failure, chronic obstructive pulmonary disease, diabetes)Previous major surgeriesCurrent prescription of medicationFurthermore, the following laboratory results will be gained:Blood cell countGlobal coagulatory function (internationalized ratio, thromboplastin time, fibrinogen levels)Parameters of renal function (creatinine, urea,)Parameters of cardiac function (troponin I, creatinine kinase, myoglobin, nt brain natriuretic peptide)Inflammatory Parameters (C-Reactive Protein, Procalcitonin)

### Perioperative management

#### Induction and maintenance of anesthesia

All patients receive the standard hemodynamic monitoring (electrocardiogram, non-invasive blood pressure, and plethysmography). Non-invasive blood pressure will be measured every three minutes by oscillometry.

Independently of the randomized study group, induction of anesthesia will be performed with fentanyl, propofol, and cis-atracurium. Dosages will be chosen according to the patient’s age and body weight as well as pre-existing diseases according to the assessment of the attending physician. After intubation, all patients are ventilated with a tidal volume of 8 ml/kg ideal body weight and with regard to the capnography (target end-tidal CO2 of 35–40 mmHg). The control group will be managed according to our SOP with the aim of an MAP > 65 mmHg. The depth of anesthesia will be measured during the whole operation with bispectral index monitoring with the goal between 40 and 60, avoiding burst suppression.

##### Intervention group

The intervention group will receive HPI-guided goal-directed therapy (GDT) using the ClearSight system. Prior to the surgery the rest cardiac index and contractility (dp/dt) will be quantified. For this purpose, the cardiac index will be measured in the preoperative night by applying the HPI ClearSight system through a study team member. If the rest cardiac index is not available throughout the night because the patient’s sleep is altered by the measurements, the awake cardiac index will be quantified until the monitoring is stopped for the night sleep of the patient. This mean baseline measurements (CI and dp/dt) will then be the target cardiac index throughout the study algorithm (Fig. 1). In case no sleep measurement is achievable, the awake measurement will be accounted as the baseline value. The perioperative study intervention period starts with the beginning of anesthesia and ends at the end of surgery. Intraoperative MAP will be maintained at least at 65 mmHg, and cardiac index and dp/dt will be individually optimized according to the GDT algorithm.

**Fig. 1 Fig1:**
[figure not shown]
Intervention group—hemodynamic treatment algorithm

During the operation, if the HPI will increases to 80% or more, the responsible anesthesiologist will follow the algorithm (outlined below) to diagnose the underlying problem.

The algorithm includes the following steps:If stroke volume variation (SVV) is ≥ 12%, a colloid bolus (250 mL) will be indicated.If the cardiac index (or dp/dt) remaines below the identified individual cardiac index, inotropy therapy will be initiated with dobutamine at 2.5 µg/kg/min and titrate for patient’s individual optimal CI (maximum dosage 10 µg/kg/min). Halve dosage of dobutamine if heart rate raises > 100 bpm. Stop infusion if tachycardia persists.Clinical relevant bradycardia will be treated by with chronotropic medication.If the cardiac index exceeds the defined individual cardiac index, or if it is treated with dobutamine, MAP > 65 mmHg (or SVR > 800) will be restored and maintained with noradrenaline.

To ensure adherence to the algorithm in the HPI group, compliance with the study protocol will be systematically monitored. Adherence will be quantified by reviewing data from the electronic patient data management system for all hypotensive events and corresponding interventions. All hemodynamic variables will be obtained directly from the HemoSphere monitor, which is connected to every patient and records data continuously at 20-s intervals. This allows for high-resolution verification of protocol compliance and ensures that all relevant interventions in relation to hypotensive events can be reliably assessed. Specifically, all interventions triggered by the Hypotension Prediction Index (HPI) will be evaluated to ensure accurate indication and the appropriateness of the subsequent therapeutic actions. A compliance ratio will then be calculated, defined as the number of correct interventions divided by the total number of HPI-triggered therapeutic actions. This ratio will serve as a metric to assess adherence to the study protocol, specifically regarding the appropriate management of hypotensive events identified by the HPI in future practice.

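### The compliance ratio measures only whether actions taken were correct; indicated responses to HPI alarms that were omitted enter neither numerator nor denominator

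*Protocol article*

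**What the plan says.** All of the relevant text is in the protocol article under Perioperative management, Intervention group, around Fig. 1.

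- **Trigger.** The duty to act is tied to the index: "if the HPI will increases to 80% or more, the responsible anesthesiologist will follow the algorithm". The steps that follow are conditional on stroke volume variation, on cardiac index or dp/dt against the individual target, on bradycardia, and on pressure or vascular resistance.
- **Review.** "Adherence will be quantified by reviewing data from the electronic patient data management system for all hypotensive events and corresponding interventions".
- **What is evaluated.** The text then narrows to actions: "all interventions triggered by the Hypotension Prediction Index (HPI) will be evaluated to ensure accurate indication and the appropriateness of the subsequent therapeutic actions".
- **Metric.** The compliance ratio is "defined as the number of correct interventions divided by the total number of HPI-triggered therapeutic actions".
- **Purpose.** "This ratio will serve as a metric to assess adherence to the study protocol". The sentence goes on to specify the management of hypotensive events that the HPI identifies.
- **Data.** The HemoSphere monitor is connected to every patient and "records data continuously at 20-s intervals". The Data collection section confirms the interval.

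The section gives no expected compliance value or threshold and defines no other adherence measure.

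**The concern.** The intervention is a response to an early warning. Adherence can fail in two ways: the response is wrong, or an indicated response is not given. The ratio sees only the first. A team that answered few of the alarms calling for action, but answered those correctly, would score as well as a team that answered all of them.

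What is at stake is the description of how far the strategy was delivered. The Limitations section says that effects should be read as those of a combined strategy of continuous monitoring, goal-directed therapy and the HPI alarm. A reader of the results will want to know how often the alarm part was acted on. A figure presented as adherence to the protocol, but blind to omissions, would answer a different question and could overstate delivery.

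**Working it through.** There is no compliance figure in the article to reproduce, so the check is algebraic.

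**Inputs**

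- From the Intervention group section: the trigger (HPI of 80% or more) and the definition of the ratio.
- Not in the documents, assumed for illustration: A = 20 alarm episodes in which the algorithm indicates an action; t = share of these that is answered; c = share of actions that is correct; one action per answered episode.

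**Step 1: the ratio as defined**

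Actions taken = A·t. Correct actions = A·t·c.

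Ratio = (A·t·c)/(A·t) = c.

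The share answered, t, cancels. If nothing is answered (t = 0), the ratio is 0/0 and undefined.

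**Step 2: adherence per indicated episode**

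Adherence = (A·t·c)/A = t·c.

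**Step 3: numbers, A = 20**

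| Share answered t | Ratio, c = 100% | Per episode, c = 100% | Ratio, c = 90% | Per episode, c = 90% |
|---|---|---|---|---|
| 10% | 100% | 10% | 90% | 9% |
| 20% | 100% | 20% | 90% | 18% |
| 40% | 100% | 40% | 90% | 36% |
| 50% | 100% | 50% | 90% | 45% |
| 80% | 100% | 80% | 90% | 72% |
| 100% | 100% | 100% | 90% | 90% |

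The two measures agree only when every indicated episode is answered. In the 40% row with c = 100%, 8 of 20 episodes are answered: 8/8 = 100% against 8/20 = 40%.

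**Step 4: several actions per episode**

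The denominator counts actions, so an episode that prompts several actions weighs more. With m actions per answered episode, the ratio is (A·t·m·c)/(A·t·m) = c. It still does not depend on t.

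**Step 5: alarms for which no action is indicated**

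The algorithm is conditional, so some alarms may call for no therapy. Take 20 alarms, 8 of them answered correctly, and let N be the number for which an action was indicated, with the 8 among them. Adherence is 8/N:

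- N = 20: 8/20 = 40%.
- N = 8: 8/8 = 100%.

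The same stated ratio of 100% is compatible with anything from 40% to 100%. The ratio alone cannot say which.

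**Step 6: does the review of hypotensive events close the gap?**

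It could reveal an unanswered alarm that was followed by hypotension. No numerator or denominator is attached to it, however, and an unanswered alarm with no hypotension after it is outside its scope.

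**The case against.** The strongest case on the other side has five parts.

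1. **Not every untreated alarm is non-adherence.** A reader might infer that each HPI alarm without therapy is a failure, and that the overstatement is always one over the share of alarms acted on. The documents do not support this. The algorithm's steps are conditional, and where no condition is met the text lists no therapy. The one-over-share rule needs exactly one indicated action per alarm. This part stands, and it decides the denominator proposed below.
2. **The use of the ratio.** A reader might infer that the ratio will be used to explain a null result, or to attribute it to the HPI. The article does not say so. The Statistical analysis section names no per-protocol population, compliance threshold or analysis that uses it. This stands: the harm is to the description of delivery.
3. **Omissions are not lost.** Untreated alarms drop out of the ratio but should remain recoverable from the 20-second recordings. This stands, and it makes the remedy cheap. It does not repair the metric.
4. **The review is not confined to hypotensive events.** A reader might infer that adherence is judged from hypotension alone. The same paragraph also evaluates HPI-triggered interventions, including whether they were indicated. That answers part of the point, but only for interventions that took place.
5. **The wording could be read differently.** The denominator might mean actions that the HPI called for, which would capture omissions, and the full protocol is not shown. However, the sentence just before it speaks of evaluating interventions that were triggered and their appropriateness, which points to actions performed. If the other meaning is intended, the definition still has to say so.

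**Conclusion.** The point holds in a limited form. The article states a specific metric, names it as a measure of protocol adherence, and defines it so that indicated but omitted responses cannot affect it. This is a stated rule that measures the wrong quantity, and so more than a detail left to another document.

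Its size cannot be given from the documents, because they report no counts of alarms, indicated actions or responses. The ratio does not depend on the share of indicated episodes answered; that follows from the definition, provided the denominator means actions performed. The contrast of 100% with 40% is illustrative and assumes that every alarm calls for exactly one action. Nothing in the article shows that many alarms will go unanswered.

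The consequence is confined to process reporting. Endpoints, sample size and the primary between-group comparison are unaffected. The change is worth making because the ratio as written could report full compliance when the strategy was only partly delivered.

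**What to change.** Redefine the adherence measure before the data are analysed:

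- **Adherence** = number of episodes with HPI of 80% or more that were handled in conformity with the algorithm within a pre-set time, divided by all such episodes in the 20-second HemoSphere record for which the algorithm indicates an action. The trial team should fix in writing how an episode begins and ends, the time window, and how an episode with several actions is scored.
- **Episodes with no action indicated**: report their number separately, outside the denominator.
- **Present ratio**: keep it, labelled as correctness of actions taken.
- **Review of hypotensive events**: keep it as a supplement, and state what figure it will produce.

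The cost is one definition and a little programming. The monitor data are already recorded, and the present ratio already requires HPI triggers to be identified. The reported adherence may be less favourable. No change to treatment, endpoints or sample size is involved.

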##### Control group

In the control group, the HemoSphere monitor will be connected to the Clearsight finger cuff but will be fully covered, and the alarms will be silenced. The responsible anesthesiologists will treat patients based on hemodynamic variables displayed on the standard monitor. No specific protocol is employed in the control group, but the target for blood pressure monitoring is to maintain a MAP above 65 mmHg. Fluid and hemodynamic therapy is based on standard clinical practice. Colloids may be administered if the attending anesthesiologist assumes a relevant fluid deficit, for example, in cases of persistent hypotension or increasing vasopressor requirements despite crystalloid infusion. Vasopressors are typically given as bolus doses; if repeated administration becomes necessary, continuous infusion may be initiated. Inotropes are rarely used in this group, as cardiac output is not routinely measured. They may be considered only in cases of suspected impaired cardiac function (e.g., relevant pre-existing disease or intraoperative echocardiographic findings).

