### Limitations

The study may face several limitations that could influence the interpretation of its future results. As a monocentric trial, the findings will reflect the practices and patient populations of a single institution, potentially limiting their generalizability. A multicenter approach could provide more comprehensive insights. Additionally, while the chosen sample size of 150 patients is calculated to detect primary outcomes, it may lack the statistical power to observe rarer complications, such as reductions in AKI or MINS. The study design includes blinding advanced hemodynamic data from the control group while providing detailed monitoring for the intervention group, which may introduce biases in clinical management due to the differing availability of information. Moreover, the intervention group in our study combines continuous non-invasive monitoring with goal-directed therapy (targeting CI and SV) and the HPI early-warning alarm; therefore, observed effects should be interpreted as the result of this multimodal strategy rather than HPI alone. Furthermore, the outcomes will depend on the ClearSight system’s accuracy and functionality, meaning that any technical inconsistencies could affect the results.

The focus on short-term outcomes may overlook the impact on long-term recovery and organ function, including sustained renal and cardiac health. Finally, the variability in patient characteristics, due to the inclusion of different types of orthopedic and trauma surgeries, could add complexity when attributing results directly to the intervention.

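### ClearSight supplies the primary endpoint and steers only the intervention arm, so ClearSight–cuff disagreement acts differently by arm, and the article sets out no check with the cuff readings

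*Protocol article*

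**What the plan says.** **Outcome signal.** The Intervention group section says: "All hemodynamic variables will be obtained directly from the HemoSphere monitor, which is connected to every patient and records data continuously at 20-s intervals". Data collection repeats the 20-second HemoSphere record. The Outcome section defines TWA and AUC of MAP below 65 mmHg without naming the device, but no other continuous source is described. In controls the monitor is connected but "will be fully covered, and the alarms will be silenced". The abstract gives the reason: "however, this will be blinded to the anesthesiologist, to ensure the comparability of the measured hemodynamic parameters".

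**Steering signal.** "The intervention group will receive HPI-guided goal-directed therapy (GDT) using the ClearSight system". For controls, "The responsible anesthesiologists will treat patients based on hemodynamic variables displayed on the standard monitor".

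**Cuff readings.** They exist in every patient: "Non-invasive blood pressure will be measured every three minutes by oscillometry" (Induction and maintenance of anesthesia).

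**Threshold.** 65 mmHg is the pressure aim in both arms and also the endpoint threshold.

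**What is conceded.** Limitations says that outcomes depend on ClearSight's accuracy, "meaning that any technical inconsistencies could affect the results", and that unequal information may bias management. The Discussion accepts that continuous monitoring in both arms would be fairer. Neither section says that device error works differently by arm. Statistical analysis describes no agreement check and no cuff-based analysis.

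**The concern.** Using one device for the outcome in both arms makes the measurement the same but not the steering. Intervention clinicians can see and correct dips in the signal that is scored. Control clinicians correct dips in another signal, and the scored one is hidden from them. Any dip that appears on ClearSight but not on the cuff is therefore treated in one arm and only counted in the other.

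At stake is the reading of a positive primary result. It could mean less hypotension, closer tracking of the device that keeps the score, or a shifted effective pressure target. The analyses set out in the article do not separate these.

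**Working it through.** The article states no figure for ClearSight–cuff agreement, so there is none to reproduce. Every disagreement value below is an assumption.

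**Step 1: expected TWA in closed form.** Suppose each arm holds its own displayed MAP at mean 75 mmHg, SD 8 (assumed). For a signal distributed N(μ, σ), the mean depth below 65 is σ·φ(z) + (65 − μ)·Φ(z), with z = (65 − μ)/σ. This ignores the one-minute minimum for an episode.

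- Signal that steers the arm, N(75, 8): z = −1.25; 8 × 0.1826 − 10 × 0.1056 = 0.405 mmHg.
- Controls on ClearSight, zero-mean disagreement SD 4: σ = √(64 + 16) = 8.94; 8.94 × 0.2135 − 10 × 0.1318 ≈ 0.59.
- The same, SD 5: σ = √(64 + 25) = 9.43; result 0.70.
- The same, SD 6: σ = √(64 + 36) = 10; 10 × 0.2420 − 10 × 0.1587 = 0.83.
- Controls on ClearSight, constant offset −3, N(72, 8): z = −0.875; 8 × 0.2721 − 7 × 0.1908 = 0.841.

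These means do not show what happens to a rank test. That depends on how the disagreement is structured.

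**Step 2: simulation by type of disagreement.** Both arms control their own steering signal equally well. "Benefit" and "harm" mean a two-sided Wilcoxon p < 0.05 in that direction, nominally 2.5% each.

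*(a) Zero mean, varying within the patient* (20-second traces, 150 min, 75 per arm):

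| Assumed SD | Benefit on ClearSight | Harm on cuff, same traces |
|---|---|---|
| 4 mmHg | 25% | 21% |
| 6 mmHg | 71% | 76% |

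A second simulation with a different model gave 53–99% benefit on ClearSight for SD 4–6, and the reverse on the cuff. The direction is consistent but the size depends on the model.

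*(b) Constant mean offset.* Let ClearSight read 3 mmHg below the cuff. Intervention patients held at ClearSight 75 are at cuff 78. Controls held at cuff 75 are at ClearSight 72. The gap is 75 − 72 = 3 on ClearSight and 78 − 75 = 3 on the cuff, so both devices show it. Scoring each simulated trial on both devices (66 per arm; patient-level disagreement SD 3 / SD 6) gave:

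| Mean offset | ClearSight | Cuff |
|---|---|---|
| −3 | benefit 97% / 80% | benefit 97% / 80% |
| −2 | benefit 71% / 47% | benefit 69% / 46% |
| 0 | benefit about 2–3% | benefit about 2–3% |
| +3 | harm 96% / 81% | harm 96% / 78% |

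A separate trace model used patient-mean SD 4, within-patient SD 10 and mean 78. It was tuned to AUC quartiles of 6, 40 and 118 mmHg·min, near the 8.5, 34.2 and 112.7 in Sample size calculation. At 75 per arm on ClearSight, and with patient-level SD 0–8, it gave 36–48% benefit at −2 and 70–83% at −3. With no patient-level spread, 41% of trials were significant at +2 and 76% at +3, none of them for benefit.

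*(c) Zero mean, stable within the patient* (same tuned model). Mean control AUC rises from 87 to 121 (SD 5) and 172 (SD 8) mmHg·min. Over the assumed 150 min that is a TWA of 87/150 = 0.58, 121/150 = 0.81 and 172/150 = 1.15 mmHg. The Wilcoxon test shows benefit in only about 4% of trials.

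**The case against.** **A constant offset is not a false difference.** A reader might infer that a small offset creates a spurious benefit although true pressure is controlled identically. The documents do not support that. If ClearSight reads lower and the intervention arm is held to it, pressure in that arm really is higher on any scale. Nor do they give a sign: an offset the other way produces apparent harm. This objection stands. What remains of (b) is attribution, and Limitations already assigns any effect to the multimodal strategy rather than to HPI alone. It does not name a shifted target.

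**Agreement between the two analyses proves little.** A reader might also infer that a benefit seen on both devices is thereby validated. Under (b) it is not, because both move together. This stands too.

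**The steering model is simplified.** Intervention clinicians also have the cuff, and their algorithm starts from HPI of 80% or more and then uses SVV, cardiac index and dp/dt. Both dilute the effect, so the percentages are illustrations and not forecasts. Dips missed between cuff readings are a genuine benefit of continuous monitoring and not an artefact.

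**A check may exist elsewhere.** The full protocol and analysis plan are not shown, so it cannot be said that none is planned. The article does, however, fix the difference in steering and leaves the MAP source unnamed in its outcome definition.

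**Conclusion.** The concern holds in limited form. The documents establish that the outcome signal steers one arm and is hidden in the other. They establish neither the size nor the sign of any disagreement.

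- Within-patient, zero-mean disagreement can produce a significant ClearSight benefit with no true difference: about 25–99% of trials at an assumed SD of 4–6 mmHg. Here no true difference means that each arm controls its own signal equally well and neither device is taken as the truth.
- A constant mean offset gives a real pressure difference whose cause could be misread. Its direction follows the sign of the offset.
- Stable patient-level disagreement with zero mean distorts mean TWA but hardly affects the planned Wilcoxon test.

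This does not invalidate the design. It limits what a positive primary result can be taken to show, and the data for a check are already being recorded.

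**What to change.** 1. In Outcome, name ClearSight (HemoSphere, 20-second data) as the MAP source for the primary endpoint.
2. Pre-specify a supportive between-arm analysis of MAP below 65 mmHg from the three-minute oscillometric readings in both arms.
3. Report by arm the paired ClearSight-minus-cuff mean difference and its within-patient SD.
4. Say in advance how these will be read. Conflicting results on the two devices point to (a). Only the paired mean difference can reveal (b). Agreement in direction should not be used as proof of the claim.
5. In Limitations, state that device disagreement acts differently by arm.

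If the unshown analysis plan already contains items 2–4, a cross-reference is enough.

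The cost is extra analysis only, with no new measurements or patients. The drawback is that three-minute sampling misses short dips and cannot apply the one-minute episode rule, so the cuff analysis can support the primary analysis but not replace it.
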